## Abstract

**Background:**

Pulmonary arterial hypertension is a rare disorder associated with poor survival. Endothelial dysfunction plays a central role in the pathogenesis and progression of pulmonary arterial hypertension. Inflammation appears to drive this dysfunctional endothelial phenotype, propagating cycles of injury and repair in genetically susceptible patients with idiopathic and disease-associated pulmonary arterial hypertension. Therapy targeting pulmonary vascular inflammation to interrupt cycles of injury and repair and thereby delay or prevent right ventricular failure and death has not been tested. Spironolactone, a mineralocorticoid and androgen receptor antagonist, has been shown to improve endothelial function and reduce inflammation. Current management of patients with pulmonary arterial hypertension and symptoms of right heart failure includes use of mineralocorticoid receptor antagonists for their diuretic and natriuretic effects. We hypothesize that initiating spironolactone therapy at an earlier stage of disease in patients with pulmonary arterial hypertension could provide additional benefits through anti-inflammatory effects and improvements in pulmonary vascular function.

**Methods/Design:**

Seventy patients with pulmonary arterial hypertension without clinical evidence of right ventricular failure will be enrolled in a randomized, double-blinded, placebo-controlled trial to investigate the effect of early treatment with spironolactone on exercise capacity, clinical worsening and vascular inflammation *in vivo*. Our primary endpoint is change in placebo-corrected 6-minute walk distance at 24 weeks and the incidence of clinical worsening in the spironolactone group compared to placebo. At a two-sided alpha level of 0.05, we will have at least 84% power to detect an effect size (group mean difference divided by standard deviation) of 0.9 for the difference in the change of 6-minute walk distance from baseline between the two groups. Secondary endpoints include the effect of spironolactone on the change in placebo-corrected maximal oxygen consumption; plasma markers of vascular inflammation and peripheral blood mononuclear cell gene expression profiles; sympathetic nervous system activation, renin-angiotensin-aldosterone system activation and sex hormone metabolism; and right ventricular structure and function using echocardiography and novel high-resolution magnetic resonance imaging-based techniques. Safety and tolerability of spironolactone will be assessed with periodic monitoring for hyperkalemia and renal insufficiency as well as the incidence of drug discontinuation for untoward effects.

**Trial registration:**

ClinicalTrials.gov: NCT01712620

## Background

### Epidemiology and natural history

The vascular injury-induced forms of pulmonary hypertension (PH), collectively referred to as pulmonary arterial hypertension (PAH), are distinct from other causes of PH such as left-sided heart failure, parenchymal lung disease with hypoxemia and chronic thromboembolic disease (Table 1) [1]. Idiopathic pulmonary arterial hypertension (IPAH) is an unexplained form of PAH where the triggering insult to the endothelium is unclear. Several diseases may manifest PAH (referred to as disease-associated PAH) that is histopathologically identical to IPAH. The underlying process responsible for these primary diseases are thought to injure the pulmonary endothelium and ultimately lead to the development of PAH (Table 1.) [1].

**Table 1 T1:** Clinical classification of pulmonary hypertension

**Group**	**Etiology**
1	Pulmonary arterial hypertension
1.1	Idiopathic pulmonary arterial hypertension
1.2	Heritable
1.2.1	Bone morphogenetic protein receptor 2
1.2.2	Activin receptor-like kinase type 1, endoglin
1.2.3	Unknown
1.3	Drug- and toxin-induced
1.4	Associated with
1.4.1	Connective tissue diseases
1.4.2	Human immunodeficiency virus (HIV) infection
1.4.3	Portal hypertension
1.4.4	Congenital heart diseases
1.4.5	Schistosomiasis
1.4.6	Chronic hemolytic anemia
1.5	Persistent pulmonary hypertension of the newborn
1’	Pulmonary veno-occlusive disease and/or pulmonary capillary hemangiomatosis
2	Pulmonary hypertension owing to left heart disease
3	Pulmonary hypertension owing to lung diseases and/or hypoxia
4	Chronic thromboembolic pulmonary hypertension
5	Pulmonary hypertension with unclear multifactorial mechanisms

PAH is two to four times more common in woman with a mean age at diagnosis of 50.1 ±14.4 years, but it may occur at any age [2]. Prior to recent advances in treatment, the median survival for all patients in the National Institutes of Health (NIH) registry was 2.8 years; the 1-, 3- and 5-year survivals were 68%, 48% and 34%, respectively [3]. With the advent of epoprostenol therapy, the 1-, 3- and 5-year survivals for patients with IPAH has improved to 87%, 63% and 54%, respectively [4], but mortality remains unacceptably high. Therefore, therapeutic approaches that modify the natural history of IPAH and disease-associated PAH have become a major focus.

### Pathophysiology of pulmonary arterial hypertension and the role of endothelial inflammation

The initial mechanisms responsible for the development of IPAH and other forms of PAH remain incompletely understood. Independent of the inciting event, endothelial dysfunction appears to play a central role both in the pathogenesis and progression of PAH [5,6]. Inflammation has been implicated as a driver of this dysfunctional endothelial phenotype, propagating cycles of injury and repair in genetically susceptible patients with IPAH and patients with disease-associated PAH [7-9]. Histologic specimens from patients with IPAH reveal the presence of inflammatory cells, including macrophages and T- and B-lymphocytes, within classic plexiform lesions that are the hallmark of PAH [7,10]. Independent of the effects on vascular remodeling, endothelial inflammation may directly impact right ventricular (RV) function [11], possibly explaining the imperfect relationship between worsening RV function despite improvements in pulmonary vascular resistance in patients on standard therapy for PAH [12].

### Nuclear receptors and inflammation

Despite strong epidemiological evidence demonstrating a female predominance in PAH, the underlying mechanisms for this gender inequality are unclear [13]. In recent animal models of PAH that simulate features of the human disease such as occlusive or angioproliferative pulmonary vascular beds with formation of plexiform lesions and endothelial disruption, female rats develop more severe PAH than males [14]. The importance of sex hormone signaling in PAH suggests a potential therapeutic role for nuclear receptor (NR) ligands and their cognate receptors. The steroid hormone receptors, including estrogen receptor-α and -β, androgen receptor, glucocorticoid receptor, mineralocorticoid receptor (MR) and progesterone receptor, are a subgroup of the NR family of transcription factors. Our laboratory is interested in investigating anti-inflammatory NR pathways that specifically target the endothelium.

MR antagonists have been widely used in patients with left-sided heart failure or left ventricular (LV) dysfunction post-myocardial infarction [15,16]. The clinical benefit of MR antagonists in these patients has been linked to poorly characterized anti-inflammatory properties and less so to their better understood diuretic or natriuretic effects [17,18]. Spironolactone, a combined MR and androgen receptor antagonist, improves endothelial dysfunction in patients with left-sided heart failure [19-21], rheumatoid arthritis [22], and in women with polycystic ovarian syndrome [23], suggesting a possible mechanism for its clinical efficacy in these patient populations. One group has suggested that spironolactone interferes with NFκB signaling in human monocytes in a non-MR dependent manner, but the molecular basis for this conclusion has not been further clarified [24,25]. In a recent study utilizing two different animal models of PH, MR antagonists demonstrated beneficial effects on aldosterone-induced pulmonary vascular remodeling, RV hypertrophy and oxidant stress [26]. Current management of patients with severe PAH and New York Heart Association/World Health Organization (NYHA/WHO) class IV symptoms includes use of MR antagonists once clinical right heart failure has developed for their diuretic and natriuretic effects [27]. Initiating therapy with spironolactone at an earlier stage of disease in patients with PAH is a novel approach to treatment and could provide benefits through anti-inflammatory mechanisms and improvements in endothelial function that might alter the natural history of PAH. To date, however, there have been no randomized clinical trials examining the safety and efficacy of MR antagonist therapy in PAH without right heart failure. *In vitro* data from our laboratory demonstrate that spironolactone suppresses NFκB-mediated inflammatory signaling in human endothelial cells (unpublished results). We are actively investigating the molecular mechanisms that mediate the anti-inflammatory activity of spironolactone and the relative contributions of MR, androgen receptor and progesterone receptor, as well as NR-independent effects.

## Methods/Design

### Objectives

Patients with PAH (that is, Group 1 PH, Table 1) without RV failure on either no medical therapy or stable medical therapy for at least 4 weeks will be recruited to the NIH Clinical Center for a randomized, double-blinded, placebo-controlled study of early treatment with spironolactone to investigate the effect of treatment on exercise capacity, clinical worsening and vascular inflammation *in vivo*. In addition, safety and tolerability will be assessed with periodic monitoring for hyperkalemia, renal insufficiency and overall incidence of study drug intolerance relative to placebo.

### Overview of study design and study population

This study adheres to the principles of the Declaration of Helsinki and has been approved by the NIH Clinical Center Deputy Ethics Counselor and the National Heart, Lung, and Blood Institute (NHLBI) Institutional Review Board (12-CC-0211). Written informed consent will be obtained from all participants at the NIH Clinical Center prior to undergoing any testing or treatment described in this protocol. Most eligible patients will be referred from Pulmonary Hypertension Specialty Clinics. At the time of enrollment, each patient will be asked to identify a primary responsible licensed practitioner who will be notified of the patient’s enrollment and made aware of the potential development of adverse study drug effects (such as hyperkalemia and renal insufficiency) during the course of the trial. If a patient does not have a physician with expertise in PH, then they will either be referred to a physician with such expertise or they will be provided ‘standard of care’ therapy at the NIH. Eligibility will be based on information obtained from our Natural History Study and from any additional information provided by the referring physician. Participants must be at least 18 years of age and must be able to provide informed, written consent for participation in this study. There is no exclusion based on race or gender. Women of childbearing potential must agree to use adequate contraception prior to and for the duration of study participation.

Eligible individuals are patients with PAH (that is, Group 1 PH, Table 1) without clinical evidence of RV failure receiving either no medical therapy or stable medical therapy for at least the past 4 weeks (defined as no new PAH-specific therapy, no change in the dose of current PAH-specific therapy and no change in NYHA/WHO functional classification). The following parameters on right heart catheterization are required to meet the hemodynamic definition of PAH: mean pulmonary artery pressure of >25 mmHg at rest, pulmonary capillary wedge pressure of ≤15 mmHg (or LV end-diastolic pressure ≤12 mmHg) and pulmonary vascular resistance of >3 Wood units (240 dyn ⋅s ⋅cm^-5^). If clinically indicated at the time of enrollment, then a right heart catheterization will be performed at the NIH Clinical Center upon study entry. Exclusion criteria are as follows:

1. Patients with WHO Group 1 PH and evidence of right heart failure as defined by:

a. NYHA/WHO class IV symptoms

AND

b. Echocardiographic evidence of severe RV dysfunction

AND

c. Clinical signs which may include, but are not limited to elevated jugular venous pressure, ascites, and lower extremity edema

2. Patients with WHO Group 1 PH and a prior diagnosis of cirrhosis with portal hypertension as evidenced by a history of ascites, hepatic encephalopathy and/or varices prior to enrollment.

3. Patients with WHO Group 1 PH and evidence of active infection. (Patients with HIV infection and two consecutive viral loads of <500 on their most recent determinations in the past 12 months will be considered to have inactive infection.)

4. Patients with WHO Group 1 PH who have taken spironolactone or eplerenone within the last 30 days.

5. Known or suspected allergy to spironolactone.

6. Pregnant or breastfeeding women.

7. Age <18 years.

8. Inability to provide informed written consent for participation in the study.

9. Chronic kidney disease defined as estimated glomerular filtration rate (eGFR) of <50 mL/min/1.73 m^2^ of body surface area. (eGFR will be calculated using the isotope dilution mass spectrometry-traceable Modification of Diet in Renal Disease Study equation and corrected for body surface area as follows: eGFR = 175 × (serum creatinine in mg/dL)^-1.154^ × (age in years)^-0.203^ × [1.212 if African-American] × [0.742 if female].)

10.  Serum potassium at the time of enrollment of >5 mEq/L or current use of potassium-sparing diuretics, angiotensin-converting enzyme (ACE) inhibitors, angiotensin II receptor blockers or drospirenone-containing oral contraceptives.

All participants will undergo baseline testing under our Natural History protocol and serial (12 and 24 weeks) testing under this protocol according to the schedules outlined in Additional file 1: Figure S1 (all time points are approximations, ±7 days). Following each interval assessment period (baseline, 12 and 24 weeks), patients will be discharged home under the care of their referring and/or primary physicians. During the study, participants are permitted to have other medications, including PAH-specific therapies, adjusted by their primary physician as clinically necessary.

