### Study endpoints

Our primary endpoint is the effect of spironolactone therapy on the change in placebo-corrected 6-minute walk distance at 24 weeks relative to baseline values and the incidence of clinical worsening in the spironolactone group compared to placebo. Clinical worsening will be defined as the addition of a new PAH-specific medication (a prostacyclin, an endothelin-1 receptor antagonist or a phosphodiesterase-5 inhibitor), dose or route escalation (that is inhaled prostacyclin changed to intravenous prostacyclin) of a current PAH-specific medication, development of right heart failure requiring hospitalization or an escalation in outpatient diuretic therapy (that is, initiation of a new diuretic or a dose escalation of current diuretic therapy), transplantation, or death.

Secondary endpoints include effect of spironolactone therapy on exercise capacity, as measured by the change in placebo-corrected VO_2_ maximum at 24 weeks relative to baseline values; effect of spironolactone therapy on plasma markers of vascular inflammation (see Table 2) and peripheral blood mononuclear cell (PBMC) gene expression profiles, comparing changes from baseline between the treatment and placebo groups; effect of spironolactone therapy on sympathetic nervous system activation, renin-angiotensin-aldosterone system activation and sex hormone metabolism, comparing changes from baseline between the treatment and control groups (see Table 2); effect of spironolactone therapy on RV function as assessed by echocardiography, magnetic resonance imaging (MRI) and N-terminal pro-brain natriuretic peptide (NT-proBNP), comparing changes from baseline between the treatment and placebo groups; and safety and tolerability of spironolactone therapy as determined by the rate of study drug discontinuation due to hyperkalemia (serum potassium ≥5.3 mEq/L), renal insufficiency (serum creatinine rise >50% of baseline), or other side effects such as breast pain and gynecomastia compared to placebo.

**Table 2 T2:** Biomarker assessment

**Markers of endothelial dysfunction**	**Neurohormonal axis**
**Adhesion molecules**	**Sympathetic activation**
sICAM-1, sVCAM-1, sE-selectin	Epinephrine, norepinephrine, arginine vasopressin
**Markers of activated coagulation**	**Renin-angiotensin-aldosterone system activation**
von Willebrand factor, thrombomodulin, sP-selectin	Renin activity, aldosterone, angiotensin II, NT-proBNP
**Cytokines and chemokines**	**Sex hormone metabolism**

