### Treatment delivery

The total duration of the treatment period will be 24 weeks. Treatment assignment will be double-blinded. Randomization will be computer-generated and participants will be stratified according to the cause of PAH (idiopathic, heritable, and drug or toxin-induced PAH versus disease-associated PAH) and NYHA/WHO classification (I or II versus III; see Table 3). Participants meeting eligibility criteria for enrollment will be randomized to either 25 mg of spironolactone or matching placebo once daily. The NIH Clinical Center Pharmaceutical Development Section will be compounding and monitoring study drug stability. Four different capsules will be prepared: spironolactone 25 mg and matching placebo, and spironolactone 50 mg and matching placebo. If the 25 mg dose of study drug is well tolerated, (that is, potassium remains <5.0 mEq/L and serum creatinine does not increase >50% from baseline at study entry) then the dose will be increased to 50 mg daily following week 6 laboratory monitoring (Figure 1).

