#### Study analysis

Participant characteristics will be summarized using contingency tables (for categorical variables), means and standard deviations for continuous variables that are approximately normally distributed (transformed if needed) or median and inter-quartile range for continuous variables that are not normal.

For the primary endpoints, changes in 6-minute walk distance (24 weeks versus baseline) will be compared between the two groups using linear mixed models (LMMs), Kaplan-Meier curves will be plotted to show the time to clinical worsening, and a log-rank test will be used to compare the two arms. Chi-squared tests or Fisher exact tests, t-tests or Wilcoxon rank-sum tests will be used to compare variables between the two arms when appropriate. The rates of study drug discontinuation between the two arms will be compared using the Fisher exact test, and a logistic regression will be considered to account for potential confounders if the two arms are imbalanced. The causes of discontinuation will be tabulated and compared if appropriate.

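### Every added or escalated PAH drug counts as clinical worsening, although untreated patients are eligible and PAH therapy may change during the trial; starts without deterioration therefore dilute a primary-endpoint component

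*Protocol article*

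**What the plan says.** All statements are in the protocol article.

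- **Eligibility** (Overview of study design and study population): participants are "receiving either no medical therapy or stable medical therapy for at least the past 4 weeks". Patients on no PAH drug can therefore be randomised.
- **Access to care** (same section): for a patient without a PH expert, "they will either be referred to a physician with such expertise or they will be provided ‘standard of care’ therapy at the NIH". The timing of such therapy relative to randomisation is not given.
- **Changes during the study** (same section): "participants are permitted to have other medications, including PAH-specific therapies, adjusted by their primary physician as clinically necessary".
- **Endpoint** (Study endpoints): the primary endpoint is the 24-week change in walk distance "and the incidence of clinical worsening in the spironolactone group compared to placebo". The definition of that second part opens with drug additions: "Clinical worsening will be defined as the addition of a new PAH-specific medication"; dose or route escalation of a current PAH drug also qualifies, as do right heart failure events, transplantation and death.
- **Analysis** (Study analysis): "Kaplan-Meier curves will be plotted to show the time to clinical worsening, and a log-rank test will be used to compare the two arms". Walk distance is compared with linear mixed models.
- **Randomisation** (Treatment delivery): "participants will be stratified according to the cause of PAH" and by NYHA/WHO class, I or II against III. Background PAH therapy is not a stratification factor.

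**The concern.** An added PAH drug is a reasonable marker of worsening when every participant is already on settled treatment, because a change then usually signals that treatment has failed. It is a weaker marker when some participants enter untreated. Their first drug may be started because a physician judges treatment due, not because the disease has advanced. The same applies to an escalation made for a reason other than deterioration.

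As defined, the component cannot tell these cases apart. Take an untreated class II patient who is randomised, does not deteriorate, and is given a first PAH drug at week 3. That patient is a clinical worsening event.

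Two things are at stake. The log-rank comparison takes in events unrelated to study drug or progression, which moves its hazard ratio toward 1. The walk comparison is also affected, because a newly started active drug falls between the baseline and 24-week tests.

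**Working it through.** **1. Does the text produce such events?** Three conditions are needed.
- An untreated patient can be randomised: yes, by the eligibility sentence.
- A PAH drug can be started after randomisation without deterioration: yes. The condition is clinical necessity, which is need-based but is not the same as worsening.
- The start is an event: yes. The definition has no deterioration criterion and no exemption for a first drug. By contrast, the diuretic component is written under the development of right heart failure.

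**2. The plan's own figure.** The only stated power is at least 84% for walk distance, at effect size 0.9 and two-sided alpha 0.05. With 50 completers, 25 per arm, the normal approximation gives Φ(0.9 × √12.5 − 1.96) = Φ(1.22) = 0.889, and the t-test gives 0.877. The figure holds as a lower bound. It does not cover clinical worsening, for which the article gives no event rate, hazard ratio or power. Everything below is therefore assumption.

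**3. Dilution of the hazard ratio.** Let p₀ and p₁ be the true 24-week worsening risks on placebo and spironolactone, and q the risk, equal in both arms, of a start unrelated to worsening. With proportional hazards and independent causes:

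HR = [−ln(1−p₁) − ln(1−q)] / [−ln(1−p₀) − ln(1−q)]

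Assume p₀ = 0.20 and p₁ = 0.10. For q, assume that 10% to 30% of participants enter untreated and that 50% to 80% of them start a drug without deteriorating: 0.10 × 0.50 = 0.05, up to 0.30 × 0.80 = 0.24.

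| q | Numerator | Denominator | HR |
|---|---|---|---|
| 0 | 0.105 | 0.223 | 0.47 |
| 0.05 | 0.105 + 0.051 | 0.223 + 0.051 | 0.57 |
| 0.10 | 0.105 + 0.105 | 0.223 + 0.105 | 0.64 |
| 0.24 | 0.105 + 0.274 | 0.223 + 0.274 | 0.76 |

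**4. A second scenario, with power.** Assume 35 per arm, 25% placebo worsening and a true HR of 0.5. Power is approximated by Φ(√(d/4) × |ln HR| − 1.96), with d the expected number of events. The last column is 70q/d; it is an upper limit, because some patients who start a drug would have worsened first.

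| q | Events d | HR | Power | Share of events that are unrelated starts, at most |
|---|---|---|---|---|
| 0 | 13.4 | 0.50 | 0.25 | 0 |
| 0.05 | 16.3 | 0.58 | 0.20 | 22% |
| 0.10 | 19.1 | 0.63 | 0.17 | 37% |
| 0.20 | 24.8 | 0.72 | 0.13 | 57% |

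**5. Chance imbalance.** If 14 of 70 patients were untreated (assumed) and allocation were 35:35, a split of 9:5 or more uneven would occur in about 37% of randomisations (hypergeometric, ignoring strata). This is ordinary sampling variation, but adjusting for the factor would remove much of its effect on the estimate.

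**The case against.** The strongest reply is that the size is unknown and may be small. The article says most eligible patients will come from pulmonary hypertension specialty clinics, so few may be untreated or lack an expert. A q of 0.24 needs both assumed shares at their maximum. The trial is described as a pilot and claims power only for walk distance. In the second scenario, power for clinical worsening is about 0.25 with no unrelated starts at all, so low contamination costs little. All of this stands, and it limits how serious the point can be.

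Three stronger readings are tempting, and the text does not support them.
- A reader might infer that the protocol plans first-line treatment for untreated participants and then scores it as failure. No such plan is set out. The referral and standard-of-care sentence does not place therapy after randomisation; therapy begun before it would fall under the 4-week stability rule.
- A reader might infer that later drug starts defeat that rule. It governs only the weeks before entry, and later changes are openly permitted, so there is no contradiction there.
- A reader might infer bias toward one arm. Treatment is double-blind, so the misclassification should be largely non-differential.

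It can also be said that reason-for-change fields and covariate lists are commonly left to the full protocol or analysis plan. That is fair for those details, but the event definition is stated in the article itself. Finally, an any-addition rule is objective, and tying it to a scheduled walk test would miss worsening treated between the visits at baseline, 12 and 24 weeks. That is a sound argument against one particular remedy, and the fix below avoids it.

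**Conclusion.** The point holds in a limited form. Followed exactly, the definition counts PAH-drug starts and escalations without deterioration as events in a primary-endpoint component, and eligibility together with permitted therapy makes such events possible. The consequence is dilution toward no effect, with added noise in the walk comparison.

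The size cannot be established from the article. The illustrative shifts, 0.47 to between 0.57 and 0.76, or 0.50 to between 0.58 and 0.72 in the second scenario, depend wholly on assumed worsening rates, an assumed q and equal q in both arms. If few untreated patients are enrolled, the effect is minor. This is a worthwhile, inexpensive improvement, not a defect that invalidates the trial.

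**What to change.** **(a) Reconcile the eligibility, permitted-therapy and endpoint passages.** For each PAH-drug addition or escalation, record the reason blind to arm. Count it as clinical worsening when the treating physician or investigator attributes it to PAH deterioration, shown by symptoms, functional class, signs or whatever tests are available, and not only by a scheduled walk test. Report the present any-addition definition as a sensitivity analysis. This changes how events are scored, not what treatment any participant may receive.

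**(b) Account for background PAH therapy at randomisation, none against any.** Enter it as a covariate in the walk-distance mixed model. The planned log-rank test takes no covariate, so use it as a stratum there, or as a covariate in a Cox model. The information should already be known from the eligibility check.

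**Cost.** One case report form field, amended endpoint wording and a small change to both primary analyses. There will be fewer counted events, and scoring will rest partly on blinded attribution. Because recruitment is under way, the amendment changes a primary-endpoint component mid-trial; it should be made, dated and justified before unblinding.

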### Individual participant stopping rules

PAH is a progressive disease and therefore clinical worsening may occur in participants during the protocol, irrespective of their treatment group assignment. Individual stopping rules for participants enrolled in the protocol include:

1. If a participant develops clinical evidence of right heart failure (which may include but is not limited to elevated jugular venous pressure, ascites and lower extremity edema) as determined by the patient’s primary physician or the investigators, then the participant will be removed from the protocol and treated for decompensated right heart failure according to standard of care.

2. If a participant deteriorates clinically, even in the absence of overt right heart failure, and the primary treating physician or the investigators feel that the addition of a MR antagonist such as spironolactone or eplerenone is clinically indicated then the participant will be removed from the study.

3. If a participant has more than one episode of serious hyperkalemia (potassium ≥5.3 mEq/L) or one episode of severe hyperkalemia (potassium ≥6.0 mEq/L), the study drug will be discontinued and the participant will be removed from the protocol.

4. If a participant develops renal insufficiency (rise in serum creatinine >50% of baseline) while on protocol, then the study drug will be discontinued and the participant will be removed from the protocol.

5. In the event that testing for serum potassium, blood urea nitrogen and creatinine is delayed for >7 days, the participant will be instructed to stop the study drug and will be removed from the protocol.

6. In any participant with a serum potassium level ≥ 5.3 mEq/L, a delay in laboratory monitoring longer than 48 hours from the specified time frame will result in removal from the protocol.

7. If while on study drug a participant develops significant breast pain or gynecomastia then the study drug will be discontinued and the participant will be removed from the protocol.

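### Exclusion criterion 1 defines right heart failure as three conditions that must all be present, which conflicts with the eligibility sentence, the randomisation strata, Table 3 and stopping rule 1

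*Protocol article*

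**What the plan says.** All of these passages are in the protocol article.

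- **Overview of study design and study population, eligibility sentence.** Eligible patients have Group 1 disease and are "without clinical evidence of RV failure receiving either no medical therapy or stable medical therapy". The sentence does not define RV failure. The Objectives section likewise describes the population as having no RV failure.
- **Same section, exclusion criterion 1.** It excludes "Patients with WHO Group 1 PH and evidence of right heart failure as defined by" three lettered items, with AND on its own line between each pair:
  - "a. NYHA/WHO class IV symptoms"
  - "b. Echocardiographic evidence of severe RV dysfunction"
  - "c. Clinical signs which may include, but are not limited to elevated jugular venous pressure, ascites, and lower extremity edema"
- **Treatment delivery.** Randomisation is stratified by cause of disease and by "NYHA/WHO classification (I or II versus III; see Table 3". There is no level for class IV.
- **Table 3.** The class IV entry includes, as part of the class description, that these patients show signs of right heart failure.
- **Individual participant stopping rules, rule 1.** "If a participant develops clinical evidence of right heart failure", the participant is removed. The rule gives the same three example signs as item c, requires neither class IV nor an echocardiographic finding, and leaves the determination to the primary physician or the investigators.

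**The concern.** The trial asks whether spironolactone helps before RV failure has developed, and criterion 1 is where the protocol draws that boundary. Because its items are joined by AND, it draws the boundary at the most advanced state only: a patient with two of the three features does not meet it. Other passages draw the boundary earlier, and differently from one another.

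Two practical things are at stake. First, consistency of screening: the eligibility sentence and criterion 1 can give opposite answers for the same patient, and the text does not say which governs. Second, randomisation: a class IV patient who passed screening would have no functional-class stratum to be placed in. Behind both is interpretation, since a population whose upper limit of severity is unclear is harder to describe as an early-disease population when the results are reported.

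**Working it through.** No sample-size, power or alpha figure enters this point, so there is no figure of the plan's to reproduce. The check is to list every combination of the three components and apply each rule in turn.

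Inputs: criterion 1 (all three needed); the eligibility sentence (no clinical evidence of RV failure); the strata (I or II, or III). One assumption is needed: that clinical evidence in the eligibility sentence means clinical signs. Stopping rule 1 supports this, because it uses nearly the same phrase and illustrates it with signs.

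| Class IV | Severe RV dysfunction | Signs | Excluded by criterion 1 | Eligibility sentence alone | Stratum exists | Rules agree |
|---|---|---|---|---|---|---|
| no | no | no | no | passes | yes | yes |
| no | yes | no | no | passes | yes | yes |
| no | no | yes | no | fails | yes | **no** |
| no | yes | yes | no | fails | yes | **no** |
| yes | no | no | no | passes, or fails through Table 3 | no | **no** |
| yes | yes | no | no | passes, or fails through Table 3 | no | **no** |
| yes | no | yes | no | fails | no | **no** |
| yes | yes | yes | yes | fails | no | yes (out under all) |

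Counting:

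- Criterion 1 excludes 1 of 8 and leaves 8 − 1 = 7.
- Of those 7, three are class IV with at least one other component missing. They have no stratum.
- Of those 7, three have signs but lack class IV, severe RV dysfunction, or both. They fail the eligibility sentence.
- One combination (class IV with signs, without severe RV dysfunction) is in both groups, so 3 + 3 − 1 = 5 of the 7 are in conflict.
- The remaining 7 − 5 = 2, class I to III without signs, agree under every rule.

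**If Table 3 is taken literally.** If class IV always comes with signs, the two rows with class IV and no signs cannot occur. Six combinations remain: one excluded, two consistent, and 6 − 1 − 2 = 3 in conflict. The conflict shrinks but does not disappear. On this reading item c adds nothing once item a is met, and for a class IV patient criterion 1 turns on the echocardiogram alone.

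**Entry compared with follow-up.** Item c and stopping rule 1 list the same example signs. At entry those signs count only together with two other conditions; during follow-up they are enough on their own. The protocol therefore uses two definitions of right heart failure under one name.

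The counts are of logical combinations, not of patients, and say nothing about how common each combination is.

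**The case against.** The strongest reply is that an exclusion list admits no one. A patient must also satisfy the eligibility sentence, and that sentence, read alone, turns away anyone with overt signs and, through Table 3, arguably anyone in class IV. On this view the strata are sound: they stop at class III because class IV was never meant to enter. This largely stands as an account of intent, and it means actual entry of such patients could be zero. It does not remove the contradiction. The eligibility sentence defines nothing, while criterion 1 says in terms that it is defining right heart failure. A screener could reasonably apply that definition to both sentences and conclude that a class III patient with ascites does not have right heart failure as the protocol defines it.

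That the article condenses a fuller protocol is no answer, because the criterion is stated in full and conflicts with other stated text.

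Several stronger readings are tempting and should not be drawn:

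- *That such entrants already meet the removal rule.* Stopping rule 1 applies when a participant develops right heart failure. For signs present at entry it shows a mismatch of definitions, not an automatic trigger, and a lower threshold for withdrawal than for exclusion is not in itself an error.
- *That any diuretic step in such a patient would count as clinical worsening.* The definition under Study endpoints can be read so that diuretic escalation counts only when right heart failure has developed.
- *That patients in need of a mineralocorticoid receptor antagonist would be held on placebo.* Exclusion 4 bars recent use of spironolactone or eplerenone, exclusion 10 bars current potassium-sparing diuretics, and stopping rule 2 removes anyone for whom such a drug is judged indicated. These soften that worry considerably.
- *That a given share of the 70 participants, or of the events, is affected.* The document gives no rate from which to work this out.
- *That the treatment comparison is biased.* Allocation is randomised 1:1, so entrants of this kind would widen the population rather than favour an arm.

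**Conclusion.** The contradiction holds. Criterion 1 conflicts with the eligibility sentence and the strata in five of the seven combinations that it leaves in, or three of five if Table 3 is read as making signs universal in class IV. It also does not match the signs-only description in stopping rule 1. This is a conflict between stated rules, not an omitted detail.

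The consequences that the documents support are limited to these: screeners may decide the same patient differently, a class IV entrant could not be placed in a stratum, and the severity limit of the study population is unclear. No power, alpha or analysis statement is affected. The number of patients involved cannot be estimated from the protocol. The conclusion rests on reading the separate-line ANDs as written and on taking clinical evidence to mean clinical signs. The Trial status section says that recruitment is under way, so the wording is already in use.

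**What to change.** Reconcile exclusion criterion 1, the eligibility sentence, the functional-class strata, Table 3 and stopping rule 1 under one definition of right heart failure. Which definition is clinically right is for the sponsor and investigators to decide. The amendment should also:

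- state explicitly whether class IV patients are eligible, so that the entry criteria and strata agree; if they are eligible, the strata need a level for them;
- if the entry and withdrawal definitions are meant to differ, say so and describe each separately.

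The cost is amendment wording and notice to those who screen. Depending on the definition chosen, eligibility may become slightly narrower than the literal text of criterion 1 allows. No change to the sample size or the planned analyses follows from the rewording itself, apart from the stratum level if class IV is declared eligible.
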